# Correlation of preoperative frailty with postoperative delirium and one-year mortality in Chinese geriatric patients undergoing noncardiac surgery: Study protocol for a prospective observational cohort study

**DOI:** 10.1371/journal.pone.0295500

**Published:** 2024-03-06

## Abstract

**Background:**

To Frailty is associated with postoperative delirium (POD) but is rarely assessed in patients undergoing noncardiac surgery. In this study, the correlation between preoperative frailty and POD, one-year mortality will be investigated in noncardiac Chinese geriatric surgery patients.

**Methods:**

This study is a prospective, observational, cohort study conducted at a single center with Chinese geriatric patients. Patients who undergo noncardiac surgery and are older than 70 years will be included. A total of 536 noncardiac surgery patients will be recruited from the First Affiliated Hospital of Shandong First Medical University for this study. The Barthel Index (BI) rating will be used to assess the patient’s ability to carry out everyday activities on the 1st preoperative day. The modified frailty index (mFI) will be used to assess frailty. Patients in the nonfrailty group will have an mFI < 0.21, and patients in the frailty group will have an mFI ≥ 0.21. The primary outcome is the incidence of POD. Three-Minute Diagnostic Interview for CAM-defined Delirium (3D-CAM) will be conducted twice daily during the 1st-7th postoperative days, or just before discharge. The secondary outcomes will include one-year mortality, in-hospital cardiopulmonary events, infections, acute renal injury, and cerebrovascular events.

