## Background

Geriatric adults often suffer from delirium, an acute disorder of attention and cognition, which can be life-threatening. Following an acute illness, surgery, or hospitalization [1], delirium often sets off a series of events that lead to institutionalization, loss of independence, increased morbidity and mortality, and high healthcare expenditure costs [2]. POD is a difficult and complex illness that typically develops 24 to 72 hours after surgery and affects 20% to 80% of geriatric individual patients [3,4]. Aging-related problems are getting worse. More significantly, geriatric patients have undergone surgery frequently over the previous 20 years. Compared to aging, more people are getting sick [5]. In addition, studies have shown that frailty is also more prevalent in the surgical group (frailty percentage 42%–50%) than in the nonsurgical aged population (frailty proportion 4%–10%) [6–8]. Therefore, it is imperative to preoperatively assess the overall health status of geriatric patients and to quickly reverse or lessen their frailty [9].

One of the biggest threats to world health in the twenty-first century is frailty, which goes beyond chronological age. The clinical syndrome of frailty is defined as “a loss of physiological capabilities and reserves in several organ systems that is accompanied by an increased sensitivity to stressors.” [10–12]. In spite of the fact that geriatric patients are equally likely to have positive postoperative outcomes as younger patients, fragile patients are more likely to have negative outcomes [13,14]. Postoperative complications can be predicted by preoperative frailty [15,16], including delirium [17,18], falls [19,20], prolonged hospitalizations [21], hospital readmissions [21], discharge to a nursing or assisted-living facility [22], and other surgical complications [16,23]. Elderly frailty is also associated with lower quality of life [8] as well as an accurate predictor of all-cause mortality [16,24,25].

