### Study implementation

All members of the research team will receive systematic training to master and use the MMSE, aCCI, mFI, BI, 3D-CAM, and CAM-ICU before the study and may only participate after passing the examination.

**Preoperative frailty assessment:** The mFI is a National Surgical Quality Improvement Gauge (NSQIP)-based 11-factor index that has been proven to adequately reflect frailty and predict mortality and morbidity [32]. The mFI is calculated by dividing the number of factors present for a patient by the number of available factors for which there are no missing data [33]. An mFI score of 0 is classified as healthy, 0–0.21 is classified as a prefrail, and ≥ 0.21 is classified as a prefrail. The index includes 11 items: nonindependent function or activity status; history of diabetes; history of chronic obstructive pulmonary disease (COPD) or pneumonia; history of congestive heart failure; history of myocardial infarction; angina pectoris, percutaneous coronary intervention (PCI), cardiac surgery; hypertension requiring medication; peripheral vascular disease or static pain; sensory disturbance; transient ischaemic attack (TIA) attack or cerebrovascular accident without sequelae; cerebrovascular accident with sequelae [34]. In this study, patients with moderate and severe dysfunction with a BI ≤ 60 are considered to be positive for item 1. The advantage is that it has been employed and is frequently used in the risk classification of various surgical operations in the NSQIP database of the United States.The majority of evaluation indexes are comorbidities, poor nutrition, metabolism, and other physical function indexes, which is a drawback.**Assessment of activities of daily living:** The patients will be assessed preoperatively by the BI evaluation form; 0–40 is classified as severe dysfunction, 41–60 is classified as moderate dysfunction, 61–99 is classified as mild dysfunction, and 100 is classified as self-care.**Diagnosis of POD:** The 3D-CAM will be used to evaluate POD twice a day (8:00–10:00 and 18:00–20:00) on the the 1^st^ to 7^th^ postoperative days. The 3D-CAM provides a brief assessment (3 orientation items, 4 attention items, 3 symptom probes, and 10 observational items) that facilitates rating of the 4 core CAM features and has a sensitivity of 95% and specificity of 94% when compared with a clinical reference standard rating in a prospective validation study in hospitalized patients [35].

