### Primary outcome

The primary outcome will be the incidence of POD.

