### Participant timeline

On the day before surgery, candidates will be scrutinized according to the inclusion and exclusion criteria. According to their mFI scores, researchers will classify the participants into the frailty group or the nonfrailty group after receiving written informed consent. We’ll keep track of every intraoperative variable.

From the first to the third postoperative day, the patients will be checked on once in the morning and once in the afternoon, and the 3D-CAM score will be taken to gauge the frequency and seriousness of delirium. On the 30^th^ postoperative day, a phone follow-up will be finished, and any issues that develop within 30 days of the procedure will be noted.

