### Statistical methods

Continuous variables will be subjected to normality tests (such as age). If the data have a normal distribution, the mean ± standard deviation will be used to represent the data. Intergroup comparisons will be made using independent-sample t tests. In the absence of a normal distribution, medians (interquartile range) will be used to express the data, and the Wilcoxon rank sum test will be applied to compare the groups. A categorical variable, such as the sex or complications, will be expressed as a frequency (percentage). We will use either the chi-square test or Fisher’s exact probability approach for intergroup comparisons.

The primary outcomes of POD will be analyzed using a logistic regression model. The correlation between weakness and POD will be calculated using odds ratios (ORs) and 95% confidence intervals (CIs).

Kaplan-Meier survival curves will be used to describe the incidence of secondary outcomes. We will use the log-rank test to compare the differences between groups. A Cox regression model will be used to analyze the influencing factors for 30-day readmissions and complications.

In order to compare the abscission rate between the two groups, the chi-square test will be used.

All statistical analyses will be conducted using the two-sided test with a p value < 0.05 considered statistically significant.

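### The protocol gives three delirium-testing windows; if testing ends at discharge, frail patients are observed longer and the planned logistic odds ratio does not allow for it

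*Protocol article*

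**What the plan says.** The primary endpoint is given in one sentence: "The primary outcome will be the incidence of POD". That a patient counts as a case after any positive test is implied, not written. The period over which this is judged appears in three forms:

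- **Abstract, Methods:** testing is "twice daily during the 1st-7th postoperative days, or just before discharge".
- **Study implementation, Diagnosis of POD:** "The 3D-CAM will be used to evaluate POD twice a day (8:00–10:00 and 18:00–20:00"), on postoperative days 1 to 7, with no mention of discharge.
- **Participant timeline:** "From the first to the third postoperative day, the patients will be checked on once in the morning and once in the afternoon".

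Under Statistical methods, "The primary outcomes of POD will be analyzed using a logistic regression model", with an OR and 95% CI. No common window and no handling of unequal days of testing are named.

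Three other statements bear on the point. The Background lists longer hospital stay among the outcomes that frailty predicts, and says that POD "typically develops 24 to 72 hours after surgery". Study implementation reports that the 3D-CAM "has a sensitivity of 95% and specificity of 94% when compared with a clinical reference standard rating". Table 1 excludes hospital stays under 3 days, and Secondary outcomes counts the stay from admission.

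**The concern.** Under the abstract's window, the number of tests depends on when the patient goes home, up to 14 tests over 7 days. By the protocol's own account the exposure lengthens the stay, so it also lengthens the period in which the outcome can be recorded. A logistic model on a yes/no outcome treats every patient as equally observed.

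Two routes then favour a higher POD count in frail patients, even with the same true risk:

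1. Delirium that starts late is recorded only in patients still in hospital.
2. Each further test is another chance of a false positive.

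Adjusting for age or type of surgery leaves the path from frailty through stay to number of tests in place. At stake is whether the primary OR can be read as an association of frailty with delirium, or partly as one of frailty with being tested.

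**Working it through.** **The plan's own effect.** From Sample size calculation, POD is 35.7% in frail and 21.7% in nonfrail patients: OR = (0.357/0.643)/(0.217/0.783) = 2.00. The stated 112 and 370 patients reproduce with a continuity-corrected two-proportion formula, and 482/0.9 = 536. This point does not affect them.

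**Maximum tests under each window.** Days 1 to 3: 3 × 2 = 6 for everyone still in hospital. Days 1 to 7: 7 × 2 = 14. Days 1 to 7 or discharge: from a few to 14, depending on stay.

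**Route 1: late onsets, perfect test, no true effect.** Recorded POD = 0.217 × Σ over days of (share of onsets on that day × share still tested that day), with the same 0.217 in both groups. The documents give neither curve, so both are assumptions. Shares still tested on days 1 to 7:

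| Gap | Nonfrail | Frail |
|---|---|---|
| Small | 1, 1, 1, .90, .80, .65, .50 | 1, 1, 1, .95, .90, .80, .70 |
| Mid | 1, 1, .95, .75, .60, .45, .35 | 1, 1, 1, .95, .90, .85, .75 |
| Large | 1, .95, .80, .55, .40, .30, .20 | 1 on all days |

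Worked case: onsets .35, .28, .17, .08, .06, .03, .03 (80% by day 3) and the mid gap. Captured share is 0.9115 nonfrail and 0.978 frail, so recorded POD is 19.78% and 21.22%, and OR = 1.09.

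| Onsets by day 3 | Small gap | Mid gap | Large gap |
|---|---|---|---|
| 90% | 1.01 | 1.05 | 1.15 |
| 80% | 1.03 | 1.09 | 1.25 |
| 60% | 1.06 | 1.20 | 1.51 |
| 43% (flat over 7 days) | 1.11 | 1.33 | 1.85 |

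The Background's typical onset at 24 to 72 hours points to the first two rows.

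**Route 2: false positives, no true effect.** With 94% specificity and independent errors, P(at least one false positive in k tests) = 1 − 0.94^k: 31% for 6 tests, 39% for 8, 58% for 14. For correlated errors I used a beta-binomial with mean 0.06 and within-patient correlation ρ. Recorded POD = p + (1 − p) × P(any false positive), with assumed true p = 15% in both groups and assumed tests of 14 (frail) and 8 (nonfrail):

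| ρ | Nonfrail | Frail | Spurious OR |
|---|---|---|---|
| 0 | 48.2% | 64.3% | 1.93 |
| 0.2 | 36.4% | 42.6% | 1.29 |
| 0.5 | 28.0% | 30.3% | 1.12 |
| 0.8 | 22.8% | 23.5% | 1.04 |

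With smaller gaps, ρ from 0.2 to 0.8 gives 1.17 to 1.02 for 14 vs 10 tests, and 1.11 to 1.02 for 10 vs 8.

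**Route 2 when a real effect exists.** Take 35.7% and 21.7% as the true rates (OR 2.00) and the same error model:

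| ρ | 8 tests in both groups | 14 frail, 8 nonfrail |
|---|---|---|
| 0.2 | 1.53 | 1.84 |
| 0.5 | 1.65 | 1.76 |
| 0.8 | 1.75 | 1.79 |

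Unequal testing raises the OR relative to equal testing, but the result still lies below the true 2.00, because false positives dilute a real difference. Only near-independent errors exceed it (2.46 at ρ = 0).

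**Effect of a day 1 to 3 window.** In route 1 with 80% of onsets by day 3, the OR falls from 1.09 to 1.01 (mid gap) and from 1.25 to 1.08 (large gap). The remainder comes from patients assumed to leave before day 3.

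**The case against.** The best counter-argument is that the premise is not settled. Only the abstract ends testing at discharge. If the Participant timeline governs, almost everyone has about six tests and the problem nearly disappears. That is correct, and it is why the conflict between the three passages comes first. It does not dispose of the point: two of the three passages say days 1 to 7, and the one that gives a discharge clause makes observation depend on stay.

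A reader might infer from the 1.93 that extra testing alone could produce the planned OR of 2.00. The documents do not support this. That figure needs independent errors over 14 tests and recorded POD of 48% and 64%, whereas the sample size section expects 21.7% and 35.7%. To bring the nonfrail rate to 21.7% with true POD of 15% and 8 tests, ρ must be about 0.88, and at 0.8 the spurious OR is already only 1.04. The 94% is reported as accuracy against a reference rating; nothing says that errors are independent across repeated tests.

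A reader might also infer that the reported OR must lie further from 1 than the truth. That is not so when a real effect exists, as the working shows.

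Two further objections stand in part. Early typical onset and the exclusion of short stays limit route 1, although a stay counted from admission does not secure three postoperative days. And sensitivity analyses are often left to an analysis plan; but the contradictory window, and a stated model that does not allow for one of its versions, are in this document.

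**Conclusion.** The point holds in a limited, conditional form. The three testing windows contradict one another and must be reconciled. If testing ends at discharge, the plan observes frail patients longer, and the logistic OR is inflated relative to equal observation.

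The size cannot be fixed from the documents, because no stay or test count by group is given. With no true effect, early onset and correlated errors, each route taken alone gives about 1.0 to 1.3. The two would act together, and I have not combined them. Values near 1.9 need flat onset with a large stay gap, or independent test errors, and should be read as upper bounds. A bias of 1.1 to 1.3 is modest beside 2.00, but under the null it favours the study hypothesis, and the planned model gives no means of detecting it. The stay curves, onset curves, test counts, true POD of 15% and correlations are all assumptions.

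**What to change.** 1. State one testing window and use it in the abstract, Study implementation and Participant timeline, including what happens at discharge before its end.
2. In Statistical methods, pre-specify an analysis of POD on days 1 to 3, the span shared by all three passages.
3. Add a discrete-time logistic model with one record per scheduled test, ending at first POD, discharge, death or day 7.
4. Tabulate the number of tests per patient by frailty group.
5. Report the 7-day and common-window ORs side by side, and call the association robust only if the common-window OR with its 95% CI also supports it.

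Length of stay should not be used as an adjustment variable, since delirium may itself lengthen the stay.

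The cost is some extra analysis of data already collected. The day 1 to 3 analysis has fewer events and so a wider interval. It does not make observation perfectly equal, because Table 1 read with the definition of stay does not guarantee three postoperative days for everyone. It equalises the number of false-positive chances between groups but does not remove their dilution of a real effect.

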**Discussion:**

This study will clarify the correlation of preoperative frailty with POD and one-year all-cause mortality in Chinese geriatric patients undergoing noncardiac surgery. Can preoperative frailty predict POD or one-year mortality? In the face of China’s serious aging social problems, this result may have important clinical value for the surgical treatment of geriatric patients.

**Trial registration:**

This protocol has been registered with ClinicalTrials. Gov on 12 January 2022 (https://clinicaltrials.gov/ct2/show/NCT05189678).

## Background

Geriatric adults often suffer from delirium, an acute disorder of attention and cognition, which can be life-threatening. Following an acute illness, surgery, or hospitalization [1], delirium often sets off a series of events that lead to institutionalization, loss of independence, increased morbidity and mortality, and high healthcare expenditure costs [2]. POD is a difficult and complex illness that typically develops 24 to 72 hours after surgery and affects 20% to 80% of geriatric individual patients [3,4]. Aging-related problems are getting worse. More significantly, geriatric patients have undergone surgery frequently over the previous 20 years. Compared to aging, more people are getting sick [5]. In addition, studies have shown that frailty is also more prevalent in the surgical group (frailty percentage 42%–50%) than in the nonsurgical aged population (frailty proportion 4%–10%) [6–8]. Therefore, it is imperative to preoperatively assess the overall health status of geriatric patients and to quickly reverse or lessen their frailty [9].

One of the biggest threats to world health in the twenty-first century is frailty, which goes beyond chronological age. The clinical syndrome of frailty is defined as “a loss of physiological capabilities and reserves in several organ systems that is accompanied by an increased sensitivity to stressors.” [10–12]. In spite of the fact that geriatric patients are equally likely to have positive postoperative outcomes as younger patients, fragile patients are more likely to have negative outcomes [13,14]. Postoperative complications can be predicted by preoperative frailty [15,16], including delirium [17,18], falls [19,20], prolonged hospitalizations [21], hospital readmissions [21], discharge to a nursing or assisted-living facility [22], and other surgical complications [16,23]. Elderly frailty is also associated with lower quality of life [8] as well as an accurate predictor of all-cause mortality [16,24,25].

Age, operation type, intensive care unit (ICU) admission, pain, and some drugs are just a few of the many recognized changeable and nonmodifiable risk factors for POD. One of the major risk factors that cannot be changed is age. Accordingly, preoperative screening for geriatric illnesses that are linked to POD and predict poor surgical outcomes is advised for patients undergoing geriatric surgery [26]. The most critical factor is frailty, which is a strong predictor of a range of poor health outcomes in the aged, including falls, disability, and dementia [10,27]. Frailty has been shown to be the most prevalent disease that results in death in geriatric patients [28], which stresses the significance of recognizing frailty in geriatric patients in clinical practice. Frailty is also an independent predictor of postoperative outcome [29]. The therapeutic value of preoperative decision-making and prognostic assessment depends on the early detection of fragile patients. Preoperative frailty has not yet been proven to be a separate risk factor for POD [30]. This study will look at the relationship between preoperative fragility and the prevalence of POD and one-year mortality undergoing noncardiac surgery.

## Methods/Design

The protocol was written in accordance with the Standard Protocol Items: Recommendations for Interventional Trials guidelines [31]; the protocol is summarised in Figs 1 and 2.

**Fig 1 pone.0295500.g001:**
[figure not shown]
Timeline and schedule for enrolment, allocation, and assessments. MMSE, Mini-mental State Examination; BI, Barthel Indexl; mFI, modified frailty index; aCCI, age-adjusted Charlson Comorbidity Index; 3D-CAM, 3-Minute Diagnostic Confusion Assessment Method; CAM-ICU, confusion assessment model for intensive care unit.

**Fig 2 pone.0295500.g002:**
[figure not shown]
Flow diagram of the study.

This is a single-centre, prospective, observational, cohort study of preoperative frailty and POD in geriatric patients undergoing noncardiac surgery. Therefore, the study was designed without intervention, randomization and blindness.

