### Data collection methods

Researchers who are responsible for data management will collect participant data. The data collection files will be standardized to ensure that all data are recorded and can be analyzed in the future. It will be necessary to have at least two researchers (an operator and a research assistant) collect data in each case, and the research assistant will be responsible for supplementing and improving the Case Report Form (CRF) form.

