According to the inclusion and exclusion criteria, patients will undergo a rigorous screening process. Researchers who have been trained and evaluated will do the preoperative and postoperative follow-up and data collecting for the chosen patients. This research is based on observation. The conclusions will reflect the significance of preoperative frailty assessment and further demonstrate which frailty index indicators are independent risk factors related to POD from the findings of multivariate regression analysis. In geriatric patients undergoing noncardiac surgery, this will serve as a basis for preventing POD.

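### The observational design is given as the reason for no blinding, but it does not prevent masking the delirium rater to frailty group, and the plan nowhere separates that rater from the person who scores the mFI

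*Protocol article*

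**What the plan says.** Methods/Design, in the text after the Fig 2 caption, calls the study a single-centre, prospective, observational cohort and draws the consequence that "the study was designed without intervention, randomization and blindness".

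Four other sections bear on who knows what, and when:

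- **Participant timeline.** On the basis of the mFI, "researchers will classify the participants into the frailty group or the nonfrailty group after receiving written informed consent". Screening takes place on the day before surgery, so the label exists before any delirium rating.
- **Study implementation.** "All members of the research team will receive systematic training to master and use the MMSE, aCCI, mFI, BI, 3D-CAM, and CAM-ICU". Everyone is trained on both the exposure and the outcome instruments, and no division of tasks is given. The same section describes the 3D-CAM as comprising "3 orientation items, 4 attention items, 3 symptom probes, and 10 observational items", and says that it "has a sensitivity of 95% and specificity of 94% when compared with a clinical reference standard rating".
- **Data collection methods.** "It will be necessary to have at least two researchers (an operator and a research assistant) collect data in each case"; of the second person it says that "the research assistant will be responsible for supplementing and improving the Case Report Form (CRF) form".
- **Discussion.** "Researchers who have been trained and evaluated will do the preoperative and postoperative follow-up and data collecting for the chosen patients".

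One section makes the group relevant during conduct: under Participants, enrolment ends once both groups have reached their projected size.

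**The concern.** The inference in Methods/Design runs two kinds of masking together. Without an allocated treatment there is nothing to conceal from patients or clinicians, so treatment masking does not arise. Keeping the outcome rater unaware of the exposure is a separate matter, and it is available in a cohort study whenever exposure and outcome are assessed at different times and could be assessed by different people. Both conditions can be met here.

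This matters because the primary outcome is rated at the bedside and half of the listed 3D-CAM items are the rater's own observations. The protocol also expects more delirium in frail patients (Sample size calculation: 35.7% against 21.7%), so a rater's expectation has a direction. If borderline observations are scored more readily as positive in patients known to be frail, the odds ratio moves away from 1 for a reason unrelated to frailty. A larger sample or covariate adjustment would not correct that.

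It is a stated design decision with a stated reason, so it is not a detail that the condensed article has left to a fuller document.

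**Working it through.** **1. The plan's own figure.** Inputs from Sample size calculation: 35.7% and 21.7% delirium, frail to nonfrail ratio 0.303, two-sided 0.05, power 0.80, dropout 10%. The pooled two-proportion formula without continuity correction gives 103 frail patients, which does not match. With continuity correction it gives 112 frail and 112/0.303 = 369.6, so 370 nonfrail. For dropout, 482/0.9 = 535.6, so 536. The stated size is reproduced. The planned odds ratio is (0.357/0.643)/(0.217/0.783) = 2.00. These figures only set the scale: masking changes no sample-size input.

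**2. Who is separated from whom.**

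| Question | Section | Answer in the text |
|---|---|---|
| Is the rater masked? | Methods/Design | No; all blinding is waived |
| Who assigns the group? | Participant timeline | Researchers, before surgery |
| Who follows patients afterwards? | Discussion | Trained researchers, pre- and postoperative work named together |
| Are roles split by instrument? | Study implementation | No; all members are trained on all instruments |
| Is the second researcher a separate rater? | Data collection methods | No; the stated duty is completing the CRF |

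The text neither says that one individual does both tasks for a given patient nor rules it out.

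**3. Illustration of the possible effect.** The amount of rater drift is assumed, because the documents give none.

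Common delirium rate under no true difference, using the stated 23.0% frailty:

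P = 0.23 × 0.357 + 0.77 × 0.217 = 0.0821 + 0.1671 = 0.249.

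Let the frail group be recorded at P + d and the nonfrail group at P, with n = 112 and 370. Then

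- OR = [(P + d)/(1 − P − d)] / [P/(1 − P)];
- rejection = 1 − Φ[(1.96·SE0 − d)/SE1] + Φ[(−1.96·SE0 − d)/SE1], where SE0 is the pooled and SE1 the unpooled standard error of the difference.

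d = 0.03:
- OR = (0.279/0.721)/(0.249/0.751) = 0.3870/0.3316 = 1.17.
- SE0 = 0.0471, SE1 = 0.0480; rejection = 0.097 + 0.005 = 0.103 (rounded after summing).

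d = 0.05:
- OR = (0.299/0.701)/(0.249/0.751) = 0.4265/0.3316 = 1.29.
- SE0 = 0.0473, SE1 = 0.0488; rejection = 0.190 + 0.002 = 0.192.

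Exact enumeration of the same test gives 0.103 and 0.190, against 0.050 for d = 0. Over-calling of 3 to 5 points in the whole group means specificity lower by 0.03/0.751 = 4.0 to 0.05/0.751 = 6.7 points among patients without delirium.

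**4. Second route, from the stated accuracy.** Take true delirium at 21.7% in both groups, sensitivity 95% throughout and specificity 94% in the nonfrail. The recorded rate in the nonfrail is 0.217 × 0.95 + 0.783 × 0.06 = 0.253. Lower only the specificity in the frail (assumed):

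| Specificity in frail | Recorded rate in frail | OR | Rejection |
|---|---|---|---|
| 0.94 | 0.253 | 1.00 | 5.0% |
| 0.92 | 0.269 | 1.08 | 6.5% |
| 0.90 | 0.284 | 1.17 | 10.6% |
| 0.88 | 0.300 | 1.27 | 17.4% |

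Both routes give the same order of magnitude.

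**The case against.** - **Same-person rating.** A reader might infer that the individual who assigns the frailty group also rates that patient's delirium. The text supports this only at team level. The point does not depend on it: with all blinding waived, a different rater could also know the label.
- **The label is needed during conduct.** A reader might infer that nobody needs the frailty group before analysis. The enrolment rule under Participants says otherwise, because running counts in both groups decide when recruitment ends. This stands, but the counts can be held by someone other than the rater.
- **The two-person arrangement.** It might be read as a ready-made split between exposure and outcome. It is not. The assistant's duty is to complete the CRF, and withholding the mFI and BI pages from that person would conflict with this duty as written. The roles would have to be redefined.
- **Limits of masking.** Several mFI items, such as stroke with sequelae, sensory disturbance or dependence, may be apparent at the bedside. It would be wrong to claim that the bias can be eliminated.
- **Structure and training.** The other 10 listed items are orientation, attention and symptom questions, four core features are rated, and staff must pass an examination. This lessens the scope for subjective scoring but does not replace masking.
- **Size.** The drift is assumed, the resulting odds ratios are well below the planned 2.00, and the rejection rates are for a two-proportion test whereas the primary analysis is a logistic regression. All of this stands; the figures illustrate and do not estimate.
- **Timing.** Trial status puts completion at the end of December 2023, before publication in March 2024. For patients already rated, only reporting can change.

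**Conclusion.** The point holds in a limited form. The reason given for waiving blinding does not cover the delirium rater, and no section separates mFI scoring from 3D-CAM rating. The primary odds ratio is therefore open to detection bias, most plausibly upward.

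The documents do not show that such bias will occur or how large it would be. Under assumed over-calling of 3 to 5 points in the frail group, and with no true difference, a spurious odds ratio of 1.17 to 1.29 and a false-positive rate of about 10% to 19% instead of 5% would result. Smaller drift gives less: a 2-point loss of specificity gives an odds ratio of 1.08 and 6.5%.

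This is a worthwhile correction to design and reporting. It does not show that the study is invalid, and it leaves the sample size at 112 and 370, or 536 with dropout.

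**What to change.** 1. In Methods/Design, keep the statement that there is no intervention and no randomization. Replace the waiver of blinding by a statement that delirium assessors are masked to mFI score and frailty group.
2. In Data collection methods, redefine the two researchers per case. One collects the mFI and BI before surgery; the other rates 3D-CAM without access to those CRF pages. Reassign the CRF-completion duty so that it does not expose the rater to them.
3. In Participant timeline, let data management, not the rater, derive the mFI group and keep the counts needed for the enrolment stop under Participants.
4. For patients already rated unmasked, report that raters were not masked to frailty group and state it as a limitation.

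The cost is rota planning and separation of CRF pages. Whether the existing staff can cover the twice-daily ratings under this split cannot be judged from the article. Masking will be partial, so the gain is a reduction in bias, not its removal.
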